- **Study Protocol**
- **Effectiveness of Reciproc system for anterior teeth with apical periodontitis: a randomized controlled pragmatic trial**
- **Proponent:**
- PhD Student: [name]
- Health Sciences Graduate Program
- Federal University of Sergipe
- **Doctoral Adviser:**
- [name]. [name]
- Department of Dentistry
- Health Campus / Biology and Health Science Center
- Federal University of Sergipe
- Aracaju
- June 2015
- **ABSTRACT**
- Single file canal preparation techniques emerged in an attempt to overcome drawbacks related to manual and continuous rotary techniques. It has shown promising results in in-vitro studies, but its effectiveness has not yet been tested in clinical studies. Hence, this proposal seeks to investigate, through an equivalency randomized controlled clinical trial, the effectiveness of the Reciproc® single file, single cone system, regarding its success rate, incidence rate of post-operative pain and PAI score changes. This trial will follow the Consort guidelines, having a parallel design and using an active treatment as control – the crown-down instrumentation technique and the lateral condensation obturation technique. Patients in need of endodontic treatment for anterior teeth due to pulp necrosis and with radiographic evidence of apical periodontitis will be randomized to receive endodontic treatment either by the Reciproc® single file, single cone system or by the crown-down manual technique with stainless steel files. Patients will be questioned about their pain levels at baseline and then 24 hours, 72 hours days and 7 days after treatment is performed. The Wilcoxon test will be used to compare treatment pain scores. Patients will be called for one- year follow-up visits in which PAI score changes and clinical signs of periapical pathosis will be ascertained. Data related to PAI scores will be submitted to the Wilcoxon test to compare treatment outcomes and to the Man-Whitney test to compare one-year follow-up scores within each treatment group. Each individual treatment will be classified as “success” if their PAI scores are 2 or lower and they show no clinical signs or symptoms of periapical disease. Success rates of each treatment and the relative risk of experimental group in relation to control will be determined. In addition, Fishers exact test will be used to compare treatment groups’ success rates. For all analyses, a 95% significance level will be used.

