- To evaluate participants’, the pupal condition will be evaluated through thermal sensitivity tests – cold and heat – and through periapical radiographs made by the paralleling technique. A clinical evaluation will also be performed (visual inspection, palpation, vertical and horizontal percussion) to identify and register the presence or absence of sinus tract, tenderness, tooth mobility and pain.
- If the occurrence of pulpal necrosis and apical periodontitis is confirmed and if the patient gives written consent to participate in the study, the baseline PAI will be recorded according with the instructions of Orstavick et al (19).
- Table 1. Periapical Index Score (19).

| - PAI SCORE | - Criteria |
| --- | --- |
| - 1 | - Normal Periapical structures |
| - 2 | - Small changes in bone structure |
| - 3 | - Changes in bone structure with some mineral loss |
| - 4 | - Periodontitis with well-defined radiolucent area |
| - 5 | - Severe periodontitis |

- In case the patient reports any sensitivity before treatment, its level will be registered according to the verbal scale detailed in table 2. If the patient does not report any pain, the score 0 will be registered, which corresponds to absence of pain.
- Table 2. Verbal pain scale (21).

| - 5-Level pain scale to evaluate pain severity: Reference Values given to patients | | |
| --- | --- | --- |
| - 0 | - No pain | - The patient feels good |
| - 1 | - Mild pain | - If distracted, he/she does not fell pain |
| - 2 | - Moderate Pain | - The patient feels moderate pain, even when concentrating on some activity |
| - 3 | - Considerable | - The patients feel very unwell but nevertheless can continue with ordinary activities of daily life |
| - 4 | - Severe pain | - The patient is forced to give up ordinary activities of daily life |
| - 5 | - Extreme | - The patient is no longer able to perform any type of activity and needs to lie down and rest |

- 5.2.4 Random sequence generation and allocation concealment
- A random list will be created using the website [www.sealedenvelope.com](http://www.sealedenvelope.com/). The treatment to be performed on each patient will be placed into opaque and sealed envelopes by a third party not involved in the study intervention. The dentists who will perform the clinical procedures will only open the envelope at the moment of the intervention.
- 5.2.5 Study interventions

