- Thirty periapical radiographs of endodontically treated teeth not included in the study will be used for calibration procedures by two independent and blinded evaluators. The evaluation of such radiographs will be repeated until intra- and inter-evaluator agreement has a Kappa coefficient higher than 0.80.
- Apical periodontitis will be classified using the initial radiography, and according to PAI scores. Bitewing film holders will be used to standardize the position of radiographs. Silicone impression material (Optosil Comfort, Heraeus Kulzer, Hanau, Germany) will be placed on the film holder, and impressions of the tooth undergoing treatment will be taken. Then, the impression will be used to place the device in the same position during the follow-up evaluations.
- The patients will be called after 12-months. New periapical radiographs will be taken, and the lesions will be reclassified according to the PAI scale. Then, the teeth will be classified as healed (scores 1 or 2); healing (reduced score compared to baseline, but higher than 2); or not healed. Teeth that are clinically asymptomatic – defined by absence of pain, tenderness to percussion and/or palpation, sinus tract, or soft tissue swelling – and present a PAI score of 1 or 2 will be classified as “success”.
- If the patients record any postoperative pain, it will be recorded using both a visual analog scale (VAS) and a verbal rating scale (VRS). For the VAS, the patient will set her/his pain level by pointing (with a pen) along a 10-cm continuous line between two endpoints (ranging from the absence of pain to unbearable pain). The distance between the marking and the border corresponding to the absence of pain will be recorded. The peak of pain at the first 24 h, as well the pain reported at 24 h, 72 h and 7 days after the end of the endodontic treatment will be recorded. Postoperative pain was also scored according to the VRS. The latter scale was used to assess the incidence of postoperative pain (scores differing from 0). The occurrence of flare-up was recorded when the patients presented severe pain and swelling following the endodontic treatment.
- 5.2.8 Blinding
- Because this is an intervention study, clinicians cannot be blinded for the procedures they will perform. The patients will not be informed of which group they are allocated to.
- 5.3 Statistical analysis

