- Baseline demographic data of the participants and clinical characteristics of the teeth included in the study will be categorized, and the absolute and relative frequencies calculated (except for PAI scores, final preparation size scores, age and follow-up time). The difference between the interventions regarding the distribution of these characteristics will be assessed by Chi-squared analysis. For PAI scores, final preparation size scores, age and follow-up time, data will be analyzed using either t-test or Mann-Whitney Rank-Sum test.
- The Wilcoxon Rank-Sum test for equivalence using two one-sided tests (TOST) procedure will be used to assess if, 12 months after the treatment, the 95% confidence intervals of the mean PAI score treatment difference falls within the pre-established equivalence limit (main outcome of interest). For all other outcomes, traditional two-sided superiority analyses will be used. The association between treatment protocol and changes on periapical status will be analyzed by Chi-squared test or by Fisher`s exact test. The success rates for each treatment protocol will be calculated, and differences analyzed by Chi-squared testing. Univariate logistic regression will used to determine any association between explanatory variables and the treatment’s success rate. Factors with a p-value < 0.1 will be included in a multivariate analysis. Odds ratios and 95% confidence intervals will be calculated.
- For all VAS data, normal distribution and possible differences between the treatments will be assessed through the Shapiro-Wilk test and t-test, respectively. Data from VRS will be analyzed through the Wilcoxon rank-sum test. The incidence of postoperative pain and flare-up will be calculated, and Chi-squared tests will be used to assess any possible association between treatment and incidence. Differences between the treatments regarding the incidence and intensity of postoperative pain will be calculated, as well as their confidence intervals at 95%. The level of significance will be set at 95% for all analyses.
- .
- **6. Scientific contributions of the proposal**

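### The protocol does not settle whether a pain-free patient scores 0 on the postoperative VAS, so the planned t-test could run on a post-randomisation subgroup; it also leaves preoperative pain unused

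*Protocol*

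**What the plan says.** Section 5.2.8 (Evaluations) opens its pain paragraph with a condition: "If the patients record any postoperative pain, it will be recorded using both a visual analog scale (VAS) and a verbal rating scale (VRS". It then lists the recording times without one: "The peak of pain at the first 24 h, as well the pain reported at 24 h, 72 h and 7 days". The VAS line is described as "ranging from the absence of pain to unbearable pain", so it can hold a zero. Of the VRS it says "The latter scale was used to assess the incidence of postoperative pain (scores differing from 0".

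Section 5.2.3 has an explicit zero rule for the preoperative verbal score: "If the patient does not report any pain, the score 0 will be registered, which corresponds to absence of pain". No matching sentence covers the postoperative scales. The abstract states, without a condition: "Patients will be questioned about their pain levels at baseline and then 24 hours, 72 hours days and 7 days after treatment is performed".

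Section 5.3 fixes the VAS analysis: "For all VAS data, normal distribution and possible differences between the treatments will be assessed through the Shapiro-Wilk test and t-test, respectively". VRS data go to a rank-sum test and pain incidence to a chi-squared test, and differences in incidence and intensity are to be reported with 95% confidence intervals. The preoperative pain score appears in none of these pain analyses. Section 5.1 makes pain a secondary outcome and admits both symptomatic and asymptomatic apical periodontitis.

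**The concern.** If site staff follow the conditional sentence as written, a patient without pain has no VAS value. The t-test then compares patients with pain in one arm against patients with pain in the other. Whether a patient has pain is itself an outcome of treatment, so randomisation no longer protects that comparison. A technique that hurts more patients, each to a similar degree, would show no VAS difference. A technique that adds mild pain in further patients would appear to hurt less.

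This bears on why pain is measured. Sections 1.1 and 1.2 argue that reciprocating files may extrude more debris and so raise both the incidence and the severity of pain, and the third specific objective in section 3.2 compares both. Without a defined population, the promised confidence interval for the intensity difference has no clear meaning. A blank VAS would also be indistinguishable from a missed contact.

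This cannot be left to an analysis plan, because it is a rule for collecting data: a score not taken within the first week cannot be recovered later.

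A smaller matter is that a baseline pain score is collected in a mixed population and then not used where it could sharpen the pain comparison.

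**Working it through.** **The plan's own figure.** The protocol gives no sample size for pain. Its 60 per arm rests on PAI (section 5.2.1: margin 0.5, SD 0.74, type I error 0.05, power 0.90, 20% for drop-out). With two one-sided tests at 0.05 and a true difference of 0:

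n = 2 × [0.74 × (1.645 + 1.645) / 0.5]² = 47.4, so 48 per arm; 48 / 0.80 = 60.

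The figure is reproduced. Pain is measured within 7 days, so up to 60 per arm may be available; 48 is the number expected at 12 months.

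**The texts side by side.**
- For scoring those with pain: the conditional sentence in 5.2.8, and the absence of a postoperative counterpart to the zero rule in 5.2.3.
- For scoring everyone: the abstract; the unconditional list of times; the no-pain end of the VAS line; and incidence defined as a VRS score other than 0, which makes sense only if zeros are recorded.

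The last item is strong for the VRS. It does not settle the VAS, because incidence is defined from the VRS alone and being asked about pain is not the same as marking a line.

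**Size if the literal reading is followed.** The protocol gives no pain rates or VAS values, so all inputs here are assumptions. Rejection rates come from 5,000 simulated trials with 60 per arm and a two-sided 5% t-test.

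| Assumed scenario | Difference, zeros kept | Rejects | Difference, pain only | Rejects |
|---|---|---|---|---|
| A: pain in 40% v 20%; VAS 3 cm (SD 1.5) if in pain | 0.40×3 − 0.20×3 = 0.60 cm (simulated 0.61) | 55% | 3 − 3 = 0 cm (simulated 0.00) | 5% |
| B: 20% at about 4 cm in both arms, plus 20% at about 1.5 cm in one arm | 0.20×4 + 0.20×1.5 − 0.20×4 = 0.30 cm | 18% | (4 + 1.5)/2 − 4 = −1.25 cm | 71% |
| C: pain in 30% of both arms; VAS 3 cm (SD 1.5) if in pain | 0 | 5% | 0 | 5% |

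In A the pain-only test would have about 60 × 0.40 = 24 against 60 × 0.20 = 12 patients. In B the sign reverses, and the reversed difference is the one more often declared significant. In C, with identical pain distributions, both versions hold their 5% level.

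**What the planned incidence test would still show.** For 40% v 20%, an uncorrected chi-squared test rejects in 59% of simulated trials at 48 per arm (49% with continuity correction) and 68% at 60 per arm.

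**Preoperative pain.** If r is the correlation between the preoperative verbal score and the postoperative VAS, adjustment multiplies the residual variance by 1 − r². The protocol gives no r. At 0.3 the factor is 0.91 (a 9% cut) and at 0.5 it is 0.75 (a 25% cut). Over a wider range of 0.2 to 0.6 the cut is 4% to 36%.

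**The case against.** The strongest reply is that the protocol never says pain is recorded solely from those who have it. The conditional sentence can be read as naming the instruments, and the rest of the text points to scoring everyone. Nothing in section 5.3 limits the VAS test to patients with pain. This stands: a reader might infer a settled rule of pain-only scoring, and the documents do not support that. What remains is that the one operative sentence on recording is conditional and no postoperative zero rule overrides it.

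A reader might also infer that excess pain from the new technique would go undetected. That does not follow. Section 5.3 plans a separate incidence test, and in a 40% v 20% scenario it has at least the power of the all-patient t-test (68% v 55% at 60 per arm). The VAS result could still contradict the incidence result, as in scenario B, so the incidence test limits the damage without removing it.

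Finally, a reader might infer that ignoring preoperative pain biases the comparison. Under randomisation it does not: chance imbalance is already reflected in the standard error. The choice of covariates is also commonly left to an analysis plan, and the baseline score is verbal, with no baseline VAS described. All of this stands, so adjustment is offered as a gain in precision and not as the correction of an error.

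**Conclusion.** The point holds as an ambiguity in the recording rule, with a possible but not certain consequence. If the conditional sentence is followed literally, the VAS t-test becomes a comparison of subgroups formed after randomisation. It can then hide a difference in mean pain (0.6 cm seen as 0) or reverse one (+0.30 cm seen as −1.25 cm). Those sizes rest wholly on assumed pain rates and scores; the mechanism does not. If staff already score every patient, the VAS comparison is sound as planned and only the wording needs repair.

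The unadjusted t-test is valid. Using the preoperative score would cut residual variance by r², or 9% to 25% at an assumed r of 0.3 to 0.5.

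Pain is a secondary outcome, and the primary PAI equivalence conclusion and its sample size are untouched. The point deserves correction because the repair is nearly free and a score never taken cannot be restored.

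**What to change.** 1. In section 5.2.8 (Evaluations), state that every patient is scored on both VAS and VRS at every postoperative time, that no pain is entered as 0 on each, and that a blank means a missing assessment.
2. In section 5.3, state that the pain comparisons include all randomised patients with pain data, in the arm to which they were allocated.
3. In section 5.3, replace the unadjusted VAS t-test with a linear model of VAS on treatment and preoperative verbal pain score, with robust standard errors, since many zeros are likely. Report the adjusted difference with its 95% confidence interval.

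While editing, reconcile the assessment times: section 5.1 lists 48 hours where the abstract and section 5.2.8 list 72 hours.

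The cost is a few sentences. No visit, instrument or patient is added, the baseline score is already collected, and the sample size does not change. Items 1 and 2 should be settled before pain data are collected. If some are already in hand, a VRS of 0 recorded at the same time would support entering a blank VAS as 0; a blank on both scales should be treated as missing.

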5. Enhance the quality of education provided to students of the graduate program in Health Sciences of the Federal University of Sergipe;
6. Produce a doctoral thesis and at least two original research articles to be published in journals with an impact factor of 2 or more.
7. **Methodology**

- 5.1 Experimental Design
- This study will be a randomized controlled pragmatic clinical trial, which will follow the CONSORT (<http://www.consort-statement.org/>) statement guidelines. It will have a two-arm, parallel design (1:1 allocation ratio equivalency). The endodontic treatments to be performed are either a combination of a single-file and single-cone (SFSC) technique using the Reciproc system (experimental group) or an association of the crown-down hand files with the lateral compaction obturation (HFLC) technique (control group). The main outcome of interest is mean periapical index score (PAI) (19) difference between the two groups 12 months after treatment. Peak of pain during the first 24 hours after treatment and postoperative pain 24, 48 hours and 7 days after treatment are the secondary outcomes.
- The trial will be based on the following PICO question:
- P (Population): patients above 18 years of age, who are scheduled for an endodontic treatment in one of the public services where the study was performed cities (i.e., Capela, Estância, Laranjeiras and Nossa Senhora do Socorro) located in the state of Sergipe (Brazil), with anterior teeth presenting pulp necrosis and radiographic evidence of apical periodontitis (symptomatic apical periodontitis, asymptomatic apical periodontitis, and chronic apical abscess) with a diameter greater than 2 mm.
- I (Intervention): A combination of a reciprocating single-file and single-cone technique using the Reciproc system.
- C (Control): An association of the crown-down technique hand files with the lateral compaction obturation technique.
- O (Outcomes): Mean PAI difference between the intervention and the control group 12 months after treatment.

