- Therefore, the research question is the following: For patients presenting anterior teeth with pulp necrosis and apical periodontitis, is there difference in the outcomes obtained with hand file instrumentation and lateral compaction obturation compared with the outcomes obtained with reciprocating single file instrumentation and single cone obturation, concerning the healing of periapical lesions and postoperative pain incidence and severity? The hypothesis to be tested is that using reciprocating single files instrumentation and single cone obturation has similar effectiveness treating apical periodontitis as hand file instrumentation and lateral compaction obturation technique. In addition, the hypothesis that both endodontic protocols result in the same incidence and severity of postoperative pain and flair-up will also be tested.
- 5.2 Method
- 5.2.1 Sample Size Calculation
- The sample size was calculated for the main outcome, defined as the mean periapical index score (PAI) difference between protocols of the apical lesion 1 year after treatment. The calculation for similarity trial used an equivalence limit of 0.5, a standard deviation of 0.74 (20), type I error of 0.05, and a power test of 0.90. Furthermore, the sample was increased by 20% to compensate for any drop-out. This resulted in 60 teeth per experimental condition.
- 5.2.2 Recruitment and eligibility criteria
- The recruited participants will be patients who are scheduled for an endodontic treatment in one of the public services where the study will take place. Patients with anterior teeth presenting pulp necrosis and radiographic evidence of apical periodontitis (symptomatic apical periodontitis, asymptomatic apical periodontitis, and chronic apical abscess) with a diameter greater than 2 mm will be invited to participate in the study. Those who agreed to participate and sign the informed consent (appendix I) form will be included in this study. Only one tooth per participant will be included in the trial. Teeth with an immature apex, any radiographic evidence of root resorption, previously treated root canal or requiring extensive prosthetic rehabilitation will be excluded. Participants presenting a pre-existing health or oral condition that placed them at risk during the trial, as well as those having generalized periodontal disease, and women who are pregnant or breastfeeding are also going to be excluded.
- 5.2.3 Baseline evaluation

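### Section 5.3 names a rank-sum TOST for the primary outcome but judges equivalence by a confidence interval for the mean PAI difference; on a 1-to-5 score the named test cannot apply the 0.5 margin.

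*Protocol*

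**What the plan says.** Protocol section 5.1 defines the primary outcome on the mean scale: "The main outcome of interest is mean periapical index score (PAI) (19) difference between the two groups 12 months after treatment". Section 5.2.1 sizes the trial on that scale: "The calculation for similarity trial used an equivalence limit of 0.5, a standard deviation of 0.74", with "type I error of 0.05, and a power test of 0.90", inflated by 20% for drop-out to 60 teeth per arm.

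Table 1 in section 5.2.3 gives PAI as five ordered categories scored 1, 2, 3, 4 and 5. No fractional score, and no averaging over the two evaluators, is described.

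Section 5.3 then puts two things into one sentence. The method is: "The Wilcoxon Rank-Sum test for equivalence using two one-sided tests (TOST) procedure will be used to assess if, 12 months after the treatment". The criterion is that "the 95% confidence intervals of the mean PAI score treatment difference falls within the pre-established equivalence limit". It does not say how a rank-sum procedure would produce that interval, or which of the two decides if they disagree.

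**The concern.** Outcome, margin and sample size all concern a difference in means, but the named test compares ranks. A rank-sum TOST applies its margin by moving one arm's scores up and then down by 0.5 and re-ranking. On whole-number scores, a move of less than one unit changes only how ties are broken. The test may therefore reach a verdict without using the size of the margin.

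At stake is the trial's main conclusion. The pattern most exposed is one where most teeth in both arms heal to a low score and one arm also has a minority of clear failures at 4 or 5. The mean moves by more than 0.5, while most pairwise comparisons between arms remain ties or near-ties.

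**Working it through.** **Step 1: reproduce the sample size.** Inputs from section 5.2.1: margin 0.5, SD 0.74, type I error 0.05, power 0.90, 20% drop-out. For a TOST on two means with true difference 0:

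n = 2 × [SD × (z(1-α) + z(1-β/2)) / margin]²

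- α = 0.05 per side: 2 × [0.74 × (1.645 + 1.645) / 0.5]² = 47.4, so 48 evaluable; 48 / 0.8 = 60. This is the stated figure.
- α = 0.025 per side (a 95% interval): 2 × [0.74 × (1.960 + 1.645) / 0.5]² = 56.9, so 57; 57 / 0.8 = 71.25, so 72. This is not the stated figure.

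The 60 per arm therefore rests on a mean-based TOST read through a 90% interval.

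**Step 2: power at 48 evaluable per arm.** SE = 0.74 × √(2/48) = 0.151, and 0.5 / 0.151 = 3.31.

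- 90% interval: 2Φ(3.31 - 1.645) - 1 = about 0.90.
- 95% interval: 2Φ(3.31 - 1.960) - 1 = about 0.82.

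**Step 3: what the rank-sum TOST does on integers.** Let X and Y be scores from the two arms. For any shift d strictly between 0 and 1, X < Y + d holds exactly when X ≤ Y, and X > Y - d exactly when X ≥ Y. The ranks, and so the p-values, do not depend on d. The test asks only whether P(X > Y) and P(X < Y) are both below one half, and ties help to satisfy that. In one simulated data set the two one-sided p-values were 0.1910 and 0.00005 at margins 0.01, 0.25, 0.5, 0.75 and 0.99 alike; they changed only at 1.0. The matching Hodges-Lehmann interval is built from whole-number pairwise differences, so it fits inside ±0.5 only by collapsing to about [0, 0].

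**Step 4: consequence if the rank test alone decides.** Simulation, 48 per arm, 0.05 per side. The distributions (percent at PAI 1/2/3/4/5) are assumptions.

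| Experimental v control | True difference | Pooled SD | Rank TOST declares equivalence | Mean TOST declares equivalence |
|---|---|---|---|---|
| 55/17/13/10/5 v 70/20/8/2/0 | 0.51 | 1.01 | about 65% | about 5% |
| 60/20/15/5/0 v 95/5/0/0/0 | 0.60 | 0.66 | 61% | 1% |
| 70/10/0/10/10 v 80/15/5/0/0 | 0.55 | 1.06 | 98% | 5% |
| 0/25/50/25/0 v 12.5/37.5/37.5/12.5/0 | 0.50 | 0.79 | 5.8% | 5.0% |

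In the first row the means are 1.93 and 1.42. In the second, 35% of trials declared equivalence by ranks although the observed mean difference was itself above 0.5. At 0.025 per side the rank test still declared equivalence in 53% (first row) and about 52% to 54% (second row). Shift-like differences of 0.55 and 0.60 gave only 2% and 1.5%.

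**Step 5: consequence if the mean interval decides.** In the first row, the 95% interval for the mean difference lay inside ±0.5 in 2.6% of trials. Requiring both the interval and the rank test also gave 2.6%.

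**The case against.** The strongest defence is the second half of the sentence. It states a confidence interval for the mean difference as the criterion, and Step 5 shows that this controls false equivalence whether it acts alone or together with the rank test. This stands, and it limits the point. A reader might infer that the 0.5 margin has no effect on the primary decision; the protocol supports that only if the rank test alone decides, which it does not say. The defence does not remove the problem, because if the interval governs, the sentence names the wrong method.

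A reader might also take the high false-equivalence rates as the expected error of this trial. The protocol does not support that either. It gives no 12-month PAI distribution, and two of the skewed scenarios have pooled SDs above the planned 0.74. In four further scenarios with difference 0.50, pooled SD 0.64 to 0.75 and scores spread over neighbouring categories, the rank test declared equivalence in 4.4% to 16.9%. An SD near or below 0.74 is no protection, however: the second row of the table has 0.66. Shape decides.

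Section 5.3 also compares success rates and periapical status, so an excess of failures would be visible. Those are superiority comparisons and do not replace the equivalence test.

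Finally, ranks are a natural choice for an ordered score. A rank-based primary analysis would be coherent, but it would need its own estimand, margin and sample size, and the protocol has none of these.

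**Conclusion.** The point holds as a mismatch between the named test and the stated criterion within the primary analysis. That a rank-sum TOST cannot apply a 0.5 mean margin to integer scores is algebra and needs no assumption about the data. How much harm follows depends on two things the protocol leaves open: which half of the sentence decides, and the shape of the 12-month scores. If ranks alone decide, false equivalence ranged from no material inflation (symmetric or shift-like differences) to about 65% in the worked scenario, and higher in a more extreme one. If the mean interval decides, there is no inflation. Because the two can disagree on the same data, the choice should be fixed before results are seen.

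The sample size is not in error for a mean-based TOST at 0.05 per side. It does not, however, deliver 90% power with the 95% interval that section 5.3 states.

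**What to change.** In section 5.3, replace the rank-sum TOST with a confidence interval for the difference in mean 12-month PAI (Welch, or a linear model with robust standard errors). Conclude equivalence only if the whole interval lies inside (-0.5, +0.5). Keep a rank-based summary, such as P(better) + 0.5 × P(tie) with its interval, as a sensitivity analysis only.

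State the interval level so that it agrees with section 5.2.1. A 90% interval (0.05 per side) matches 48 evaluable and 60 per arm at 90% power. If the 95% interval is kept, restate the power as about 82% with 48 evaluable per arm; restoring 90% would take 57 evaluable, or 72 per arm.

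The cost is a sentence or two and no new data. The downside is some power when the arms are truly identical. In one scenario with SD 0.79 it was about 85% for the mean-based test against 89% for ranks. The gap was wider in two more skewed scenarios with SDs of 0.84 and 0.82 (78% v 91%, and 81% v 98%), and reversed in a symmetric one with SD 0.71 (92% v 88%). The rank test's advantage in the skewed cases comes with its failure to apply the margin, so it is not a reason to keep it.

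### Under the 95% CI rule in section 5.3, the planned 60 teeth per arm give about 81–84% power after the allowed drop-out, not the stated 90%, and the alpha per one-sided test is never given

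*Protocol*

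**What the plan says.** Protocol section 5.2.1 (Sample Size Calculation) gives the inputs for the primary outcome, the difference in mean PAI at 12 months. The margin is set by "The calculation for similarity trial used an equivalence limit of 0.5", the SD is 0.74, and the error rates are "type I error of 0.05, and a power test of 0.90". For losses, "the sample was increased by 20% to compensate for any drop-out". The result: "This resulted in 60 teeth per experimental condition". The section does not say whether the 0.05 applies to each one-sided test or is two-sided, and it gives no assumed true difference.

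Protocol section 5.3 (Statistical analysis) specifies a Wilcoxon rank-sum equivalence test by the two one-sided tests procedure, used to judge whether "the 95% confidence intervals of the mean PAI score treatment difference falls within the pre-established equivalence limit". It closes with: "The level of significance will be set at 95% for all analyses". The abstract gives the significance level in the same form.

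**The concern.** TOST with alpha on each side is equivalent to asking whether the 100(1 − 2 × alpha)% confidence interval lies inside the margins. TOST at 5% per side therefore goes with a 90% CI, and a 95% CI goes with 2.5% per side. Section 5.3 names the 95% CI. Section 5.2.1 gives 0.05 with no sidedness.

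Two things are at stake. First, the 90% power promised for the only primary outcome may not hold under the decision rule that will be applied. Second, a data set can satisfy TOST at 5% per side and still have a 95% CI that crosses a margin. Section 5.3 mentions both TOST and the 95% CI, and section 5.2.1 a type I error of 0.05, so the primary conclusion could turn on which of them the analyst follows.

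**Working it through.** **Inputs.** From section 5.2.1: margin 0.5, SD 0.74, type I error 0.05, power 0.90, 20% for drop-out, 60 per arm. From section 5.3: 95% CI within the margin. Assumption, because the protocol gives no figure: true difference 0.

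**Formula for n per arm (normal theory).** n = 2 × (SD/margin)² × (z for alpha + z for beta)², where 2 × (0.74/0.5)² = 4.3808. For equivalence at zero difference both one-sided tests must succeed, so beta is halved and z for 90% power is 1.645. If beta is not halved, z is 1.282.

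**Reproducing the 60.**

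| Alpha per side | Beta | n evaluable | n/0.8 |
|---|---|---|---|
| 5% | halved | 4.3808 × (1.645 + 1.645)² = 47.4, so 48 | 60 |
| 2.5% | halved | 4.3808 × (1.960 + 1.645)² = 56.9, so 57 | 71.25, so 72 |
| 5% | not halved | 4.3808 × (1.645 + 1.282)² = 37.5, so 38 | 47.5, so 48 |
| 2.5% | not halved | 4.3808 × (1.960 + 1.282)² = 46.0, so 47 | 58.75, so 59 |
| 2.5%, solved with the t distribution | not halved | 47.01, so 48 | 60 |

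Two routes give exactly 60: 5% per side with beta halved, and 2.5% per side with beta not halved and a t-based solution. The only variant that delivers 90% power under a 95% CI rule (2.5% per side, beta halved) gives 72, or 57 × 1.2 = 68.4, so 69, if the 20% is simply added on. Neither is 60.

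**Evaluable numbers after the planned loss.** If 20% of those randomised are lost, 60 × 0.8 = 48 remain. If 20% was added on top of the required number, 60/1.2 = 50.

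**Power.** SE = 0.74 × √(2/n); power = 2 × Φ(0.5/SE − z) − 1, with z = 1.645 for the 90% CI and 1.960 for the 95% CI.

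- n = 48: SE = 0.151 and 0.5/SE = 3.31. The 90% CI gives 2 × Φ(1.665) − 1 = 90.4%. The 95% CI gives 2 × Φ(1.350) − 1 = 82.3%.
- n = 50: SE = 0.148 and 0.5/SE = 3.38. The 95% CI gives 84.4%.
- n = 57: the 95% CI gives 90.0%.
- n = 60 (no losses): SE = 0.135 and 0.5/SE = 3.70. The 95% CI gives 91.8%.

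A t-based calculation lowers the 95% CI figures by about one point or less: 81.2% at 48, 83.4% at 50 and 91.3% at 60.

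**Disagreement between the two rules.** At 48 per arm and true difference 0, the gap between 90.4% and 82.3% is 8.1 points (about 9 with the t distribution). That is the share of trials of truly equal treatments that would pass TOST at 5% per side and fail the 95% CI.

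**The case against.** The strongest reply is that nothing in the protocol mentions a 90% CI or a one-sided 5%. A type I error of 0.05, a 95% CI and a significance level clumsily written as 95% all fit one familiar convention: 5% two-sided. On that view the planner used the 95% CI throughout, and the 60 comes from 1.960 with beta not halved and a t-based solution. This stands as far as it goes. A reader might infer from 48/0.8 = 60 that section 5.2.1 must have used 5% per side, but the document does not support that, because a second reconstruction gives the same number. It does not rescue the power, however: leaving beta unhalved is itself a sizing error for equivalence at zero difference, and the result is the same 48 per arm and the same 82%.

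A reader might also say that the threshold is stated in three incompatible ways. That goes too far. The closing sentence of section 5.3 is a slip for 5%, not a third rule.

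It is also fair to object that 82% is not a single fixed answer. With 50 evaluable it is about 84%, and with complete follow-up about 92%. But the protocol plans for 20% loss, and the 90% it states should hold after that loss.

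Finally, the plural wording about confidence intervals could be meant as two one-sided 95% bounds, which would equal a 90% CI. The text does not say so, and if that was meant it needs to be written.

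**Conclusion.** The point holds in this form: under the decision rule written in section 5.3, power is about 81–84% at the 48–50 evaluable teeth per arm that remain after the planned drop-out, against the 90% stated in section 5.2.1. The 90% needs 57 evaluable per arm by normal theory. The shortfall does not depend on how the 60 was derived.

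A reader might infer that the mismatch makes a false claim of equivalence more likely. It does not: a 95% CI rule is stricter than TOST at 5% per side. The harm is a greater chance of missing true equivalence (about 18% instead of 10% at 48 per arm) and a primary criterion that can be read in two ways.

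The figures assume a true difference of 0, SD 0.74 and normal-theory analysis. The planned test is a Wilcoxon TOST on a five-level score, whose power may differ. A true difference other than 0 would lower power under either rule.

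**What to change.** Before outcome data are seen, state the alpha for each one-sided test and the matching CI level, in the same terms, in sections 5.2.1 and 5.3. Either of these would do:

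- Keep the 95% CI (2.5% per side) and restate the power as about 82% at 48 evaluable per arm, or about 84% at 50, with the assumed true difference of 0 and the meaning of the 20% allowance made explicit.
- State TOST at 5% per side with the 90% CI, for which 60 randomised and 48 evaluable per arm give about 90% power. This is less strict than the CI rule now written, so it should be recorded as a deliberate choice.

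In section 5.3 and the abstract, change the significance level from 95% to 5%.

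The cost is wording only, with no additional patients. The first option means reporting a less favourable power figure. Keeping both the 95% CI and 90% power would instead require 57 evaluable per arm, that is 69 to 72 randomised per arm depending on how the 20% is applied.
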